## Methods/design

### Program outline of “WellBe-LINE”

The text-based self-care intervention program “WellBe-LINE,” which is customed for employees in MSEs, will be set in the LINE app (commonly used SNS chat tool in Asian countries) based on evidence-based psychological contents. One text message will be sent once per week and includes a website link (URL) for more information. Figure 1 presents an outlook on the message. The portal website (https://wellbeing-kokoro.com/) contains more than 100 articles on mental health, comprising topics about problem solving [37], acceptance and commitment therapy [38], self-compassion [39], sleep hygiene [40], cognitive behavioral therapy for insomnia [41], and physical activity [42]. Figure 2 presents the procedures for starting the program and the intervention schedules.

**Fig. 1 Fig1:**
[figure not shown]
Outlook of “WellBe-LINE”

**Fig. 2 Fig2:**
[figure not shown]
Procedures of starting “WellBe-LINE” and schedule of the intervention

### Personalization

A systematic review found that personalization is a key characteristic that promotes attractiveness and acceptability of mobile health interventions [43], through reducing end-users’ acquisition costs. Since lack of awareness of mental health is one of the challenges at MSEs [44], personalization potentially lowers the hurdles to use the program. Personalizing programs are effective at creating changes in health behavior [20], maximizing effectiveness despite the low intensity of the program. We provide 16 scenarios according to the 16 groups (gender × four age categories × psychological distress [K6 ≥ 5, or K6 < 5]) by screening check when participants started the program. Supplementary File 1 presents detailed information about the personalized program. “WellBe-LINE” provides messages in order of rank, from highest to low (week 1 to 8). Supplementary File 2 reports the final personalized scenario for the 16 groups. The efficacy of the “WellBe-LINE” itself has not been examined.

### Study design

In the feasibility study, a one-repeated-measure (pre-post) design will be used. Measurements will be taken at baseline (pre) and 8 weeks afterwards (post). Data collected will then be used to further refine the intervention, recruitment, procedures, strategy for disseminating, and power of a subsequent cluster RCT, which is a hybrid type 2 trial. This study protocol was approved by the Research Ethics Committee of the Graduate School of Medicine, Faculty of Medicine, University of Tokyo (2021190NI-(1)). The trial registration is available elsewhere (UMIN000046960).

### Participants

At the organizational level, companies with fewer than 50 employees will be recruited. At the individual level, employees over 18 years old will be recruited, regardless of their employment contract (e.g., part time). As this study examines the implementation of preventive programs for all employees, no further exclusion criteria are needed. Individuals not using LINE, without intentions to use LINE, or without devices will not be potential participants, while they will be informed about this research.

### Recruitment and procedure

To activate MSEs’ employers/managers, we will use a pre-existing trustful pipe with the MSEs. Five licensed social insurance consultants (recruiters), who are patient public involvement (PPI) members, recruited MSEs that they had a relationship with. Recruiters provide the research information and invitation to demo program (short version of “WellBe-LINE” which finishes in 1 week). If the invited company is interested in participating in the research, the recruiter will provide contact information for researchers. The researchers will then coordinate with the employers/managers on the date of the online meeting (described in the next paragraph).

After the meeting, researchers provide one poster and one original clear file for each employee. Using a template, researchers will also e-mail employees to invite employees to participate in the program. The researcher will provide one “code” for each company. Employers/managers inform employees about the present research by the way they fit the company (e.g., e-mail, posters, and other ways of appealing them). Employees who participate in the program must enter the code after registering for the program via their personal LINE account. Research details will then be explained on the LINE chat, and they will provide their concert by pushing the button to start answering the baseline survey. Employees select their sex and age categories. They also answer six questions about psychological distress (measured by K6). The program automatically recognizes their characteristics (sex × age × distress [5 + high or low]) and starts the program. Employees informed the sensitive information (i.e., the private account information of LINE, psychological distress) will be securely handled by The University of Tokyo under ethical approval and will not be disclosed to the company they are employed through the announcement from the employers/managers and the printed paper material (poster). This study will include individuals with exceeding psychological distress threshold; however, it is justified following two aspects: (i) the program serves as a universal prevention and (ii) high scores of psychological distress are not the same as the psychiatric disorders, instead the reducing the scores is worth in primary preventive interventions.

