#### Health outcome

Users’ psychological distress

Psychological distress will be measured using K6 (Kessler 6) [51, 52]. Respondents will be asked to report how frequently they had experienced the following six symptoms in the past 4 weeks: felt nervous, hopeless, restless or fidgety, worthless, depressed, and felt that everything was an effort. Response options include “none of the time,” “a little of the time,” “some of the time,” “most of the time,” and “all of the time. Scores range from 0 to 24. The Japanese version of the K6 exhibits good reliability and validity [53]. K6 works well as the CIDI Short Form in identifying cases of clinically significant mental disorders [52]. Scores over 5 are judged as having moderate psychological distress and can be used as a cutoff point for high or low distress [54, 55]. Reduction of the scores of psychological distress is a commonly used outcome in preventive interventions in the mental health field because it leads to reducing the risk of incidence of psychiatric disease [56].Work performance (HPQ)

Work performance will be evaluated using one item of the WHO Health and Work Performance Questionnaire (HPQ) [57]. Participants will then be asked to rate their overall work performance over the past 4 weeks. Items are scored on a 10-point scale ranging from 0 (worst) to 10 (best), with high scores indicating good work performance. The Japanese version of the HPQ exhibits good reliability [58].Work engagement (UWES-3)

In the ultra-short form of the Utrecht Work Engagement Scale, three items (UWES-3) will be used to assess work engagement [59]. The UWES-3 consists of three subscales (i.e., vigor, dedication, and absorption) with each of one item. The UWES-3 is a self-reported 7-point rating scale (0 = never; 6 = everyday). The mean score of the three UWES subscales, and total score is computed by adding the scores and dividing the sum by the number of items in each subscale. The Japanese version of the UWES-3 exhibits good reliability and validity [60].Job satisfaction

Job satisfaction will be measured using one item from the Brief Job Stress Questionnaire (BJSQ) [61] on a 4-point Likert scale. Higher scores indicated higher job satisfaction.Euthymia

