#### Analysis of other quantitative data

Health outcomes will be evaluated using a paired *t*-test between pre-(T1) and post-intervention (T2) according to protocol. The effect sizes and 95% CIs will be calculated using Cohen’s *d* only for those who completed the post-intervention questionnaire. For subgroup analysis, we will conduct the same analysis in the subgroup divided by program completion (completer/non-completer) and satisfaction (satisfied/unsatisfied). Statistical significance will be defined as *P* < 0.05. IBM SPSS Statistics® version 28 will be used for all analyses.

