### Limitation

This study protocol has several limitations. First, the sample size may not be adequate to detect significant effectiveness in reducing psychological distress owing to the pilot nature of this study. Second, this study protocol lacks a control group; the true impact of the implementation strategy can only be determined in the next step. Third, generalizability of the study findings is limited owing to its challenges in the recruitment process. As with the definitive trial, only the MSEs which have high interests in health promotion can be the potential participants through the current recruitment process. Future studies could engage and recruit MSEs with low interests in health promotion may be required in studies with another research focus. Fourth, individual-level penetration may be affected by personal beliefs about mental health issues in the workplace (e.g., social desirability [71], fear of stigmatizations [72], concerns about negative impact at the workplace [73]). Thus, factors not related to the implementation strategy can be considered if the outcomes are evaluated. Fifth, digital interventions risk marginalizing vulnerable groups, such as people with difficulty using devices or without internet access. Ensuring the opportunity to provide the program for all employees is essential in future consideration. Sixth, we will not provide any additional supports to participants with high psychological distress since it is justified under the aim of primary prevention and the contents are relevant to reduce distress, but there still be a potential risk to make conditions worse. Seventh, this feasibility study will collect many exploratory items from participants to utilize the findings in future implementation research. Still, it may cause participants’ burden, resulting in the response bias. Although authors limit the items to as few, the potential burden should be acknowledged. Eighth, fidelity of implementation strategies is evaluated using one simple question, instead of using systematic approach, such as a checklist. Other actions of employers/managers to be achieved through the online lecture should be defined after this feasibility trial to develop a checklist.

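### The article names highly distressed users as a group that may worsen, but its planned subgroups include none by entry K6

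*Protocol article*

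**What the plan says.** **Eligibility.** The Participants section admits adult employees and states that "no further exclusion criteria are needed". Recruitment and procedure says that people above the distress threshold will be included, for two reasons: (i) "the program serves as a universal prevention", and (ii) "high scores of psychological distress are not the same as the psychiatric disorders", with the added argument that lowering scores is worthwhile in primary prevention.

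**The K6.** The Health outcome section says "Scores range from 0 to 24" and "K6 works well as the CIDI Short Form in identifying cases of clinically significant mental disorders". On the cut it says: "Scores over 5 are judged as having moderate psychological distress and can be used as a cutoff point for high or low distress". The Personalization section instead divides users at K6 ≥ 5 against K6 < 5. With gender and four age categories this gives the 16 scenarios, so the K6 stratum is set for each user when the program starts.

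**Risk and objective.** The sixth limitation says that users with high distress get no additional support and that "there still be a potential risk to make conditions worse". The fifth objective is that the program does no harm to users' psychological distress.

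**Analysis.** Health outcomes, K6 included, are compared before and after by paired *t*-test, with effect sizes only for those who answered the post-intervention questionnaire. On subgroups: "we will conduct the same analysis in the subgroup divided by program completion (completer/non-completer) and satisfaction (satisfied/unsatisfied"). Process outcome lists five iOSDMH harm items for users and the LINE block rate, without saying how either is to be broken down.

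**The concern.** The article identifies one group of users whose condition might worsen and makes absence of harm on distress an objective. It then chooses subgroups that cannot show whether that group fared worse. Completion and satisfaction are both known only after exposure and may themselves be consequences of a bad experience. The one baseline variable that marks the group is collected for every user who starts the program, and is already split in two, but has no role in the planned analysis.

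Reason (ii) for open entry does not remove the concern. If the K6 performs as the Health outcome section says, the high scorers will include probable cases, even though no single high score amounts to a diagnosis.

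The feasibility data are meant to refine a cluster RCT, and adverse events are to guide alternative strategies before it. Without a breakdown, eligibility for that trial would be settled with no separate summary for the group in question.

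**Working it through.** The article states no figure on this point, and it says that a formal sample size calculation is not required, so there is nothing to reproduce. The check has two parts.

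**1. Do the passages conflict?**

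- Recruitment and procedure: a high score is not the same thing as a disorder.
- Health outcome: the scale is good at finding cases.

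The second describes screening performance and the first says that a positive screen is not a diagnosis. Both can be true of one scale. The Limitation text discloses a residual risk and contradicts neither. What follows from the three together is narrower: the high stratum contains probable cases, the article regards high-distress users as possibly at risk, and no planned split isolates them.

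The stratum definition does conflict. A score of exactly 5 is high under K6 ≥ 5 (Personalization) and not high under a cut of over 5 (Health outcome).

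**2. How much could pooling hide?**

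From the article: at most 200 employees; assumed participation 45–65%; 60% as the company-level target. Everything else here is an assumption.

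*Harm items.* Assume 60% registration, 60% answering at follow-up, 40% with K6 ≥ 5, and harm in 10% of the high stratum and 0% of the low.

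- Respondents: 200 × 0.60 × 0.60 = 72
- High stratum: 0.40 × 72 = 28.8, about 29
- Harmed: 0.10 × 29 = 2.9, about 3
- Pooled rate: 3/72 = 4%; within the high stratum: 3/29 = 10%
- Pooled rate in general = share × 0.10, so a share of 20–50% gives 2–5%

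Exact 95% intervals are 2–27% for 3/29 and 1–12% for 3/72. They overlap widely.

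*Mean K6 change.* Suppose a smaller, severely distressed group (share s of 3–10%, assumed) worsens by 3 points while all others improve by 0.5. Pooled mean change = (1 − s)(−0.5) + s(3):

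| s | Pooled mean change |
|---|---|
| 3% | −0.395 |
| 5% | −0.325 |
| 10% | −0.15 |

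A negative value is improvement, so the pooled mean looks favourable throughout.

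*What a split could show for that smaller group.* With 45–65% registering and 70–100% answering (retention assumed), respondents number from 200 × 0.45 × 0.70 = 63 to 200 × 0.65 = 130. At 3–10% that is about 2 to 13 people. If none reports harm, the one-sided 95% upper bound, 1 − 0.05^(1/n), is 78% for n = 2 and 21% for n = 13. A split can describe such a group but cannot establish safety in it. A cut at 5 would not isolate it in any case, since it does not separate moderate from severe distress.

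**The case against.** A reader might infer that the eligibility rationale and the K6 description contradict each other, and that open entry is therefore unjustified. The documents do not support this. A screening scale can find cases well without a high score being a disorder. Reason (i), universal prevention, is untouched by anything said about the K6, and the Participants section gives the same aim of a program for all employees. The sixth limitation states the risk openly. Disclosure is not inconsistency, although it does not measure the risk either.

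A reader might also infer that harms will be analysed only in pooled form. The article does not say so. It lists the harm items without describing their tabulation, and its subgroup sentence concerns the tests of health outcomes. A fuller protocol or analysis plan may exist. What can be said is that the article does fix its subgroups, and entry K6 is not among them.

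Three further objections stand in part:

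- The objective concerns harm to distress, whereas the iOSDMH items also cover such matters as time consumption and physical symptoms. They do include mental symptoms, and they avoid the regression-to-the-mean problem of a within-stratum K6 mean, but they answer the objective only indirectly.
- Data on harm will exist: users, managers and recruiters are all asked. The gap is in the breakdown, not in the collection.
- The sizes above are assumed. Nothing in the article shows that the high stratum is a minority, and on the illustrative counts the stratum and pooled intervals overlap.

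**Conclusion.** The concern holds in a limited form. The article sets a no-harm objective on distress and names high-distress users as possibly worsening without added support, yet fixes only subgroups defined after baseline. Pooled summaries could then look acceptable while that group does badly: a pooled harm rate of 2–5% against 10% in the stratum, or a pooled K6 improvement of 0.15 to 0.40 points while a small severe group worsens by 3. These sizes rest on assumed stratum shares, follow-up response and harm rates, and they show what is possible, not what is expected. That harms would be reported only in pooled form is inferred. Reason (ii) for open entry does not settle the matter; reason (i) stands, and eligibility itself is not shown to be wrong. This is a cheap improvement that bears on safety and on planning the next trial, and it corrects no contradiction other than the wording of the K6 cut.

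**What to change.** 1. In Analysis of other quantitative data, add a descriptive table by entry K6 stratum giving each of the five iOSDMH harm items, non-response at follow-up and the LINE block rate, with counts, denominators and exact confidence intervals. Non-response and blocking matter because users who worsened and left would be absent from the questionnaire results.
2. State that the high-stratum results will be considered when the cluster RCT is planned.
3. State that within-stratum mean K6 change will not be read as benefit or harm: users grouped by a high entry score will tend to score lower later, and those with a low score higher, through regression to the mean.
4. Reconcile the stratum definition between Personalization and Health outcome, and use one definition throughout.
5. Clarify the wording of Recruitment and procedure, Health outcome and Limitation so that they read together: a high score is not a diagnosis, high scorers will include probable cases, and inclusion rests on the universal-prevention aim. No entry limit or support rule is proposed here.

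**Cost.** A few sentences and one table from data already to be collected, provided that blocking can be linked to a user's entry stratum, which the article does not say. The drawback is small numbers per stratum, so the table is descriptive, without tests, and an absence of reported harm in it must not be taken as evidence of safety.

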### Online meeting with employers/managers (implementation strategy)

Licensed social insurance recruiters engage in the recruitment process to motivate relevant employers and managers to participate in the study. After obtaining agreement, researchers will provide 30–45 min of online semi-structured lectures (meetings) with employers and managers via zoom to determine the situation at the company and provide knowledge about behavioral changes and an effective way to invite employees for participation and attain high penetration. A previous qualitative study suggested that fundamental factors influencing the implementation of workplace health promotion in SMSEs entail the leadership engagement of employers [7]. Table 1 presents and justifies the contents of the semi-structured lecture with implementation strategy specification guidelines introduced by Proctor et al. [45] for each component. Semi-structured lectures will then be conducted using Microsoft PowerPoint. Psychological techniques for engaging employees are based on classical behavioral psychology related to motivation theory [46–49] and processing fluency related to health information [50].

**Table 1 Tab1:** Specification of the implementation strategy per Proctor et al.’s framework (reference [44])

Domain	Strategy 1: Recruitment by licensed social insurance consultants	Strategy 2: Online semi-structured lecture for employers/managers
Actor(s)	Licensed social insurance consultants (cooperators of researchers)	Researchers in the University of Tokyo
Action(s)	Introduce this research to relevant employers/managers of MSEs	Provides online semi-structured lecture via Zoom for 30–45 min
Target of the action	Employers/managers of MSEs agree to participate in this research and to attend the online lecture from researchers in the University of Tokyo	Employers/managers of MSEs announce the intervention “WellBe-LINE” for employees in an effective manner to encourage them to participate as much as possible
Temporality	At licensed social insurance consultants’ most convenient time (e.g., e-mail, poster, and online meeting) Researchers provided tools for licensed social insurance consultants to support the introduction of this study protocol - YouTube (https://www.youtube.com/watch?v=IBEq7ZsWJmc) (https://www.youtube.com/watch?v=E1Y7jU3JO5Q) - Poster - E-mail template	Before announcement in the workplace for employees via Zoom for 30–45 min Contents - Self-introduction and research explanation (5 min) - Importance of mental health measures at MSEs (5 min) - Easy way to improve employees’ mental health (10 min) - Three psychological tips for engaging employees to participate mental health interventions (15 min) - Q and A (5 min) Determining the company’s culture through interview and consulting the strategy to attract employees (5 min)
Dose	No restriction for the number of times to introduce this research	Once before company announcement for 30–45 min
Outcomes affected	Employers/managers’ acceptability, and appropriateness	Employees’ penetration (primary), appropriateness Employers/managers’ acceptability, appropriateness, and fidelity
Justification	Lack of knowledge about the impact of employees’ mental health on business [8] and not understanding the necessity of an appropriate approach [10] prohibits MSEs to adopt the intervention. Familiar licensed social insurance consultants can work as a stakeholder to motivate employers/managers of MSEs to take actions by introducing this research with customed explanations	Fundamental factors that influence the implementation of workplace health promotion in MSEs were the leadership engagement of employers [7]. Educating stakeholders is a possible recommended strategy if leadership engagement can be barriers in the context [27, 28]

*MSEs* micro- and small-sized enterprises

### Measurements

Outcomes will be measured using online self-report questionnaires and interviews with participants (employees), employers/managers, and licensed social insurance consultants (recruiters). Table 2 presents outcomes measured for each stakeholder.

**Table 2 Tab2:** Quantitative measures, stakeholders, questionnaire assessment points, system detection, and interviews

	Users (employees)		Employers/managers	Licensed social insurance consultants (recruiters)
	Pre (T1)	Post (T2)	Post (T2)	Post (T2)
Implementation outcome of implementation strategies (system detection)				
Penetration (individual level)		✓		
Implementation outcome of implementation strategies (interviews)				
Fidelity			✓	✓
Implementation outcome of implementation strategies (questionnaire)				
Cost			✓	✓
Implementation outcome of the program (questionnaire)				
Acceptability		✓	✓	✓
Appropriateness		✓	✓	✓
Feasibility		✓	✓	✓
Process outcome (system detection)				
Friend block rate		✓		
Process outcome (questionnaire)				
Uncomfortable experience/harms		✓	✓	✓
Adherence		✓		
Health outcome (questionnaire)				
Psychological distress (K6)	✓	✓		
Work performance (HPQ)	✓	✓		
Work Engagement (UWES-3)	✓	✓		
Job satisfaction	✓	✓		
Euthymia	✓	✓		

